### Savings accounts

While the girls groups provided capacity building in money management, budgeting and savings, the provision of a bank account was designed to provide a mechanism for knowledge and skills to be operationalized in practice. The bank account, provided to girls who would not otherwise typically have access to financial services, was hypothesized to reinforce girls’ money management skills, promote economic asset building, grow a culture of savings, facilitate economic independence and provide assets in cases of emergencies or other basic needs. Savings accounts, as opposed to micro-credit, were used as studies had shown in other settings limited results for such programs [20] and that micro-credit was not an appropriate first exposure to formal financial services for vulnerable adolescents [21]. Savings accounts, when appropriately designed for adolescents, had been shown in other contexts to improve financial literacy, increase the self-efficacy and savings behaviours [22]. Even in resource poor environments among vulnerable populations, savings accounts were found to increase savings and improve positive opinions about HIV prevention methods [23].

The bank account component was implemented in partnership with the National Savings and Credit Bank of Zambia (NatSave). The AGEP “Girls Dream” savings account provided adolescent girls a formal place to store money. The girls who were eligible for the savings account were provided an orientation in the girls’ group sessions and a field trip was organized to the nearest NatSave branch to provide additional information and to open accounts. Girls who were under the age of 18 years were required to have co-signatories present at the account opening. The bank account was specifically tailored to the financial needs of the girls, with a very low minimum opening balance of KW 2.5 (US $0.50) and the ability to deposit or withdraw funds with no fees. The girls who opened accounts could deposit on their own, although for girls under age 18 years the accounts required their co-signatories to withdraw funds. While no direct financial resources in the form of grants or loans were provided to AGEP girls, market research based on focus group discussions conducted during the pilot period suggested that adolescent girls had a variety of sources of income that may be used to build their savings, including cash from parents, paid piecemeal work, agricultural production, selling goods made and transactional sex [24].

## Intervention population

As noted previously, AGEP was designed to serve a minimum of 10,000 vulnerable adolescent girls in Zambia aged 10 to 19 in ten sites located within four of the ten provinces of Zambia. The study provinces and the number of sites per province were selected purposefully through discussions with the donor regarding representation of the target population and consideration of the feasibility of operating AGEP while also conducting a randomized evaluation. Study sites within provinces were selected randomly from a sampling frame of potential sites, anchored to proximally-located health and banking facilities. The sampling frames of potential sites for urban and rural areas were developed separately. For urban areas, a list of high-density residential compounds was created, and sites selected randomly from the list, while in rural areas sites were randomly selected among areas that met the following conditions: that they were located within 15 km from a health facility and within 65 km of a NatSave bank branch.

AGEP was also designed to draw participants who expressed multiple levels of vulnerability through their residential location and the socio-economic characteristics of their households. To avoid over-representing girls in AGEP who have already experienced the outcomes that were to be prevented by the programme (early marriage, becoming pregnant, dropping out of school), these indicators were not directly used to identify vulnerability. Instead, an indicator of vulnerability was created using whether girls were behind in school for their age as a proxy, which also permits characterization of the vulnerability of girls younger than those who already have been married, pregnant or dropped out of school. Conceptually, the measure captures adolescents who are at risk of adverse outcomes, given the primacy of education in a child’s life at these ages. Early in the school-going process, many children fall behind in school due to late entry, repetition of grades, and temporary withdrawal from school; all of these events are a reflection of some degree of personal and household vulnerability. The information used to develop the measure of vulnerability was collected along with other household socio-economic characteristics via a household survey in all study clusters, which was subsequently used as a sampling frame to determine eligible girls for participation in the programme with the most vulnerable girls selected from the list to receive invitations to participate.

## Evaluation methods and design

The objective of the AGEP evaluation was to implement a rigorous randomized design to more confidently attribute the changes in girls’ lives to their participation in AGEP. It was expected that the programme would have a positive impact on the longer-term demographic, reproductive and health outcomes of participating adolescents. It was also expected that the impact of the programme on these longer-term outcomes would be mediated through a set of individual assets or skills that the girls acquire through the programme. Given that the AGEP evaluation has multiple components that may lead to improved outcomes, the study was designed and statistically powered to evaluate the impact of each of these components on adolescent girl outcomes, independently for rural and urban areas.

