### Randomised cluster design

The AGEP evaluation was designed as a multi-arm randomised cluster trial where clusters within the ten study sites were randomised to receive different combinations (arms) of AGEP. The experimental and control arms of the study are displayed in Table 3, along with their associated components. Clusters assigned to the first intervention arm were assigned only the weekly girls’ group sessions. Clusters in the second intervention arm were assigned the health voucher in addition to the weekly girls’ group sessions, while clusters in the final intervention arm were assigned all components, including the bank account. The multi-arm evaluation provided for a rigorous assessment of the marginal benefit, as well as the incremental cost-effectiveness of each additional component of the intervention. All girls selected for participation in AGEP within a cluster were assigned to the intervention that was randomly selected for that cluster; girls in clusters for the control arm received neither interventions nor placebo exposures.

**Table 3 Tab3:** Randomisation arms of AGEP

Study arm	AGEP components
Intervention arm 1	Weekly girls group mentor-led sessions
Intervention arm 2	Weekly girls group mentor-led sessions + health voucher
Intervention arm 3	Weekly girls group mentor-led sessions + health voucher + bank account
Control	No components of the AGEP intervention

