The minimally detectable effect sizes were estimated for comparison of each programme component against the control; estimates of effect sizes were not obtained for comparisons between the intervention arms themselves as little prior information was available to guide such an estimation approach. Given a total of ten study sites, it was determined that a total of 40 clusters per arm (four clusters per arm per site) and 20 participants per cluster was the most efficient combination. Baseline (control) estimates of study indicators by age group and residential status were obtained from the 2007 Zambia Demographic and Health Survey [26]. Statistical power of 0.80 and an alpha coefficient of 0.05 were set, while the effect size variability was fixed at 0.00, as analyses would control for site fixed effects [25]. Table 5 provides estimates of prevalence in the control sample and minimal detectable effect sizes, by outcome and study stratifications.

**Table 5 Tab5:** Estimates of prevalence in the control and minimally detectable effect sizes in percentage points (pp) of programme impact by age-cohort and by rural and urban stratifications

	Total^a^		Rural^b^		Urban^b^	
	Younger	Older	Younger	Older	Younger	Older
Ever had sex	40%, ± 10 pp	82%, ± 9 pp	47%, ± 14 pp	89%, ± 11 pp	34%, ± 13 pp	75%, ± 13 pp
Ever married	15%, ± 6 pp	63%, ± 10 pp	19%, ± 11 pp	76%, ± 13 pp	10%, ± 8 pp	48%, ± 14 pp
Ever given birth	16%, ± 6 pp	70%, ± 10 pp	18%, ± 10 pp	83%, ± 13 pp	13%, ± 8 pp	54%, ± 14 pp
Completed grade 7	61%, ± 10 pp	60%, ± 9 pp	43%, ± 14 pp	41%, ± 15 pp	79%, ± 11 pp	85%, ± 9 pp
Completed grade 9	28%, ± 10 pp	38%, ± 10 pp	11%, ± 11 pp	17%, ± 13 pp	45%, ± 15 pp	64%, ± 14 pp
Ever use of modern contraception	15%, ± 8 pp	55%, ± 7 pp	15%, ± 12 pp	55%, ± 14 pp	15%, ± 12 pp	55%, ± 15 pp
HIV prevalence	6%, ± 4 pp	12%, ± 6 pp	6%, n/a ^c^	7%, n/a ^c^	6%, n/a ^c^	19%, ± 10 pp
HSV-2 prevalence	21%, ± 8 pp	26%, ± 8 pp	21%, ± 11 pp	26%, ± 12 pp	21%, ± 11 pp	26%, ± 12 pp

*Notes*: Younger cohort members are expected to be ages 14–18 at endline; older cohort members are expected to be ages 19–23 at endline. All estimates assume alpha of 0.05, power of 0.80, and site fixed effects

^a^For each age cohort estimates are based on: 10 sites, 4 clusters per arm per site (40 clusters per arm), and 10 subjects per cluster

^b^For each age cohort estimates are based on: 5 sites, 4 clusters per arm per site (20 clusters per arm), and 10 subjects per cluster

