^c^Not powered at 0.80 to detect programme impact

The sample size calculations indicated that 3200 girls would be needed at the end of the study to assess all key study impact indicators: 800 girls (within 40 study clusters) in each of the three AGEP arms and in the control arm. An additional 400 girls (within 20 clusters) were designated to be sampled for urban areas in nearby high-density components. These girls and clusters were designed to serve as external controls given the potential for contamination between AGEP and control girls within the same site. Never married girls were targeted at baseline as a significant proportion of older girls would have already experienced the key outcomes that were meant to be impacted by the programme. To achieve the target sample of 3600 girls at the end of the study, the sample size was inflated for non-eligibility and non-response at baseline, attrition from the cohort and refusals for biological specimen collection. Thus, the final estimated sample to be collected at baseline was 7200 or 4800 in AGEP clusters, 1600 in internal control clusters and 800 in external control areas.

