### Analysis

The primary objective of the evaluation is to assess the impact of AGEP on adolescents’ intermediate empowerment and longer-term outcomes using the above-noted hypothesis as test criteria. Important as well, analysis will be conducted to understand the underlying processes by which change occurred in the key areas of interest. As a first approach for assessing the impact of AGEP on empowerment and longer-term outcomes, an intent-to-treat analysis (ITT) will be conducted using the original randomised assignment to study arm as the primary indicator of impact. The average treatment effect of the programme on the adolescents in clusters randomised to AGEP relative to girls in clusters randomised to the control will be empirically assessed. The analysis will estimate models that are both unadjusted and adjusted for baseline covariates; both approaches accounting for strata and intraclass correlations within clusters. To accommodate for any baseline differences between AGEP and control clusters that may exist in the outcomes, a difference-in-differences (DID) calculation will be made for each indicator. The mid-term assessment after Round 3 focused on the immediate and mediating indicators as primary outcomes, while in the final assessment after Round 5 the mediating and longer-term outcomes will be the empirical focus.

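### The claim of power for each component, separately in rural and urban areas, is unsupported for the voucher and bank account, because detectable effects were calculated only against control

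*Protocol article*

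**What the plan says.** Under Evaluation methods and design, the study is described as "designed and statistically powered to evaluate the impact of each of these components on adolescent girl outcomes, independently for rural and urban areas".

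Under Randomised cluster design (and Table 3), the arms build on one another. "Clusters assigned to the first intervention arm were assigned only the weekly girls’ group sessions", and "Clusters in the second intervention arm were assigned the health voucher in addition to the weekly girls’ group sessions"; the third arm adds the bank account to both. Neither the voucher nor the account is ever given without the groups, and the account is never given without the voucher.

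Under Research population and sample sizes, "The minimally detectable effect sizes were estimated for comparison of each programme component against the control". The same sentence goes on to say that "estimates of effect sizes were not obtained for comparisons between the intervention arms themselves as little prior information was available". Table 5 gives detectable effects by age cohort for the total sample and by residence. It leaves HIV blank for rural younger, rural older and urban younger girls, with the note "Not powered at 0.80 to detect programme impact".

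Under Analysis, the effect to be estimated is the "average treatment effect of the programme on the adolescents in clusters randomised to AGEP relative to girls in clusters randomised to the control".

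**The concern.** With nested arms, arm 2 v control estimates groups plus voucher, and arm 3 v control estimates all three together. Only arm 1 v control isolates a single component. The contrasts that isolate the other two are those for which the protocol says no effect sizes were obtained. Describing the calculated contrasts as a component against control is accurate for the groups and inaccurate for the voucher and the account.

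This matters because the increments are the stated reason for four arms. The design section promises the marginal benefit of each additional component, the health voucher hypothesis is about an effect beyond the groups alone, and the economic evaluation rests on incremental cost-effectiveness. A reader who relies on the power statement could take a null increment as good evidence that an add-on contributes nothing. The by-residence wording adds a second problem, since for HIV it fails even against control in most strata.

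**Working it through.** **1. The plan's own figures.** 4 arms × 40 clusters × 20 girls = 3,200, as stated. Per age cohort (Table 5 notes), 40 × 10 = 400 girls per arm in total and 20 × 10 = 200 per arm in a rural or urban stratum.

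**2. Confirming what Table 5 measures.** Inputs from the protocol: alpha 0.05, power 0.80, control rates. Assumptions: two-sided test, and an ICC of 0 to 0.05 because none is given.

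- Effective n per arm = n / (1 + 9 × ICC). The divisor runs from 1 to 1.45.
- SE = √{[p₁(1−p₁) + p₂(1−p₂)] / effective n}.
- Detectable effect: the Δ that solves Δ = (1.960 + 0.842) × SE.
- Power = Φ(Δ/SE − 1.96).

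Ever married, older cohort, one arm v control, reduction:

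| | Control rate | Table 5 | ICC 0 | ICC 0.02 |
|---|---|---|---|---|
| Total | 63% | 10 pp | 9.7 | 10.6 |
| Rural | 76% | 13 pp | 12.8 | 13.9 |
| Urban | 48% | 14 pp | 13.7 | 14.8 |

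The stated values fit a single arm v control with a small ICC. An exact match cannot be checked without the ICC.

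**3. Which contrast isolates what.**

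| Component | Isolating contrast | Detectable effect calculated? |
|---|---|---|
| Girls groups | Arm 1 v control | Yes |
| Voucher | Arm 2 v arm 1 | No |
| Bank account | Arm 3 v arm 2 | No |

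**4. Size of the gap (illustration).** Arms are equal in size, so arm 2 v arm 1 uses the same 400 or 200 girls per arm. Assume arm 1 has already moved by the full Table 5 effect: total 63 − 10 = 53%, rural 76 − 13 = 63%, urban 48 − 14 = 34%. The 5 pp increment is also an assumption; the protocol gives none.

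At ICC 0, detectable further reduction:
- Total, 53% to 43.15%: SE = √(0.4944/400) = 0.0352; Δ = 2.802 × SE = 9.8 pp.
- Rural, 63% to 49.2%: SE = √(0.4830/200) = 0.0491; Δ = 13.8 pp.
- Urban, 34% to 21.6%: SE = √(0.3936/200) = 0.0444; Δ = 12.4 pp.

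At ICC 0, power for 5 pp:
- Total, 53% to 48%: SE = 0.0353; Φ(1.416 − 1.96) = 29%.
- Rural, 63% to 58%: SE = 0.0488; Φ(1.024 − 1.96) = 17%.
- Urban, 34% to 29%: SE = 0.0464; Φ(1.078 − 1.96) = 19%.

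Repeating with effective n divided by 1.45 (ICC 0.05):

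| | Detectable increment, ICC 0 to 0.05 | Power for 5 pp, ICC 0 to 0.05 |
|---|---|---|
| Total | 9.8–11.8 pp | 29–22% |
| Rural | 13.8–16.6 pp | 17–13% |
| Urban | 12.4–14.7 pp | 19–14% |

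**5. Sensitivity to arm 1's rate.** If arm 1 had moved by only half the Table 5 effect (58%, 69.5%, 41%), the same formulas give 9.8–11.8, 13.4–16.2 and 13.2–15.7 pp. The assumed arm 1 rate changes little in the older cohort.

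**6. HIV by residence.** Of the four residence-by-age cells in Table 5, only urban older has a detectable effect (19%, 10 pp). The other three carry the note that they are not powered.

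**The case against.** The best defence is that the sample-size section discloses the limitation and that equal arms leave every increment estimable. Both points stand. The sample size and randomisation are unaffected, and the fault lies in what the power statement claims.

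It can also be said that the reason given is fair, since the survey used for planning supplies control rates and an arm 1 rate was not available. This is partly right: arm 1's rate is an extra unknown. A range could still have been shown, because detectable effects are calculated precisely when effect sizes are unknown, as was done against control.

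Four stronger readings are tempting, and the document does not support them.

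- **That no contrast isolating the add-ons is named anywhere.** The Analysis section takes the hypotheses as its test criteria and uses assignment to study arm. The girls groups hypothesis refers to an indicator for the groups-only arm, the voucher hypothesis is framed as an effect beyond the groups alone, and the economic evaluation compares the add-ons with groups only. Only arm 3 v arm 2 goes unnamed, and a formal list of contrasts is commonly left to the analysis plan.
- **That the statement that "3200 girls would be needed at the end of the study to assess all key study impact indicators" is contradicted by the HIV note.** That sentence makes no claim by stratum, and Table 5 gives HIV effects for both total columns (4 and 6 pp).
- **That the Discussion repeats the power claim.** It speaks of a design intended to assess added value and does not mention power.
- **That null increments will be reported as coming from a powered test.** Nothing says so. It is a risk created by the wording.

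**Conclusion.** The concern holds as a contradiction within the protocol, and no unseen analysis plan could remove it: power is claimed for each component by residence, while detectable effects exist only for comparisons with control. For the voucher and the account the claim has no calculation behind it. For HIV it fails by residence in three of four strata even against control.

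The illustration suggests that, for ever married in the older cohort, an add-on would have to achieve roughly what Table 5 requires of a whole package, on top of whatever the groups achieve. These figures rest on a two-sided test, an assumed ICC of 0 to 0.05, an assumed arm 1 rate and, for the power figures, an assumed 5 pp increment. They should not be carried over to the younger cohort or to other outcomes, where base rates differ.

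**What to change.** - **Evaluation methods and design:** say that the study was powered to compare each intervention package with control, that comparisons between intervention arms were not part of the power calculation, and that HIV is not powered by residence except in the urban older stratum.
- **Research population and sample sizes:** describe the calculated contrasts as each intervention arm, not each component, against control. Add between-arm detectable effects for each outcome, calculated over a stated range of arm 1 rates and ICC. The values above are an illustration for one outcome and should not stand in for that calculation.
- **Analysis:** state that the add-on effects are estimated as arm 2 v arm 1 (voucher) and arm 3 v arm 2 (account), separately from the pooled AGEP v control effect. Report null increments with confidence intervals and not as results of a powered test.

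The statement of the 3,200 girls needed and the Discussion need no change. The cost is some rewording and a short calculation, with no new data and no change to the design. The downside is a weaker stated power claim.

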### Randomised cluster design

The AGEP evaluation was designed as a multi-arm randomised cluster trial where clusters within the ten study sites were randomised to receive different combinations (arms) of AGEP. The experimental and control arms of the study are displayed in Table 3, along with their associated components. Clusters assigned to the first intervention arm were assigned only the weekly girls’ group sessions. Clusters in the second intervention arm were assigned the health voucher in addition to the weekly girls’ group sessions, while clusters in the final intervention arm were assigned all components, including the bank account. The multi-arm evaluation provided for a rigorous assessment of the marginal benefit, as well as the incremental cost-effectiveness of each additional component of the intervention. All girls selected for participation in AGEP within a cluster were assigned to the intervention that was randomly selected for that cluster; girls in clusters for the control arm received neither interventions nor placebo exposures.

**Table 3 Tab3:** Randomisation arms of AGEP

Study arm	AGEP components
Intervention arm 1	Weekly girls group mentor-led sessions
Intervention arm 2	Weekly girls group mentor-led sessions + health voucher
Intervention arm 3	Weekly girls group mentor-led sessions + health voucher + bank account
Control	No components of the AGEP intervention

A cluster in the AGEP evaluation was delineated by Census Supervisory Areas (CSAs) that were compiled by the Zambia Central Statistical Office (CSO) for the 2010 national census. CSAs contained approximately 750 households in urban areas and 300 households in rural areas, although the average number of households varies considerably as population densities vary geographically. CSAs in urban areas were spatially relatively small, perhaps a few hundred metres long and wide, while CSAs in rural areas encompassed multiple kilometres. The assignment of CSAs to the experimental and control arms was conducted through a random selection process at a public lottery. The public lottery was conducted to maximize the transparency and community acceptance of AGEP. Local political and community leaders were invited to participate in the lottery, conducted at a centrally-located public facility. The lottery was conducted via a two-step selection process in which a CSA was first randomly selected for participation among all CSAs in the site and then an AGEP arm assigned through a second random selection process.

